### Outcomes

#### Primary outcome

As mentioned, the most important thing in a couple's decision to have children is the intention to do so and a positive attitude towards it, so:Change the behavior of couples to the operation and maintenance phase according to the TTM after the procedureChange to a positive attitude toward having a baby.

#### Secondary outcomes

Increase awareness among couples about complications related to delaying childbirthIncreases the couple's sense of reproductive controlImprove the capacity of couples to cope with the spiritual standards of societyIncrease couples' preparedness to make informed fertility decisions.

### Data collection

A questionnaire designed by researchers will be used to assess the impact of this intervention on people's attitudes and subjective norms. This questionnaire is administered to assess the three components of attitude, subjective norms, and perceived behavioral control and to determine how the change process is carried out in four stages: before the intervention (S0), immediately after the intervention (S1), 1 month after the intervention (S2) and 6 months after the procedure (S3).

The questions prepared for this study will be designed based on: Research objectives, two mentioned models, and teaching content. Once designed by the researcher, it will be sent to specialist teachers and their validity and reliability will be assessed. Questions in the S0 phase are filled in person at the clinic, but to allow people to better receive questions and answers without the need to visit the clinic, the questions asked in the questionnaire will be sent online in the later stages. This Iranian online system is called Porsline, and at an agreed time, a link to the survey is sent to participants, and the researcher monitors their responses by phone.

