### Trial design

This study is a parallel group clinical trial. The TTM and TPB are used for training and measuring outcomes. The participants are childless couples who have been married for at least 2 years and are in the pre-contemplation and contemplation stages of having children. A diagram of the research process is shown in Fig. 1. After the intervention, their attitudes, subjective norms, and perceived level of control over childbearing behavior will be compared with before the intervention, to determine whether the interventions lead couples out of the pre-contemplation stage to later stages or not. The duration of this study is approximately 2 years from the beginning of the training to the end of the follow-up (6 months after the intervention). This study was approved by the Ethics Committee (Ethics Code: IR.TUMS.FNM.REC.1402.013) of Tehran Medical University. Informed consent is completed by all participants after an explanation of the objectives of the study, the research process, and the follow-up period.

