#### Trans-theoretical model questionnaire (TTM)

At the beginning of the study, to find out whether the person meets the criteria to enter the study or not, the participant must fill out a questionnaire about the stages of change, and whether they are in the pre-contemplation or contemplation stage, it is included in the study. This questionnaire is designed based on the stages of the change model and includes 7 questions to determine which stage the person is in. After the intervention, each participant's level of change toward the next steps in behavioral intentions will be measured using this questionnaire according to specific steps.

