### Sample size

To provide a power of 95% with a 99% confidence interval using the following formula and considering the mean and standard deviation of intention to have based on the findings of a similar study by Moghaddam et al. [36]. The sample size was estimated at 12, and then considering 20% attrition, we plan to recruit 15 couples per group and a total of 30 couples study participants.$$n=\frac{{( {z}_{1-\frac{\alpha }{2}}+ {z}_{1-\beta } )}^{2} ({s}_{1}^{2}+ {s}_{2}^{2})}{{({\mu }_{1}- {\mu }_{2})}^{2}}=\frac{2.1664 \times 14.82}{2.6896}=\frac{32.106048}{2.6896}=11.93 \cong 12$$

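### Baseline is completed in person and every follow-up online, so within an arm the before-versus-after change cannot be separated from a change of mode; the between-arm difference in change is not biased by a shift common to both arms

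*Protocol article*

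**What the plan says.** Under Data collection, the protocol article schedules a baseline assessment (S0) and three later ones: directly after the intervention (S1), at 1 month (S2) and at 6 months (S3). For baseline, "Questions in the S0 phase are filled in person at the clinic". After that, "the questions asked in the questionnaire will be sent online in the later stages", through a survey platform named Porsline: "a link to the survey is sent to participants, and the researcher monitors their responses by phone". The mode schedule is given once, with no distinction between arms. The Abstract lists three assessments rather than four; on either schedule, only baseline is in person.

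Under Trial design, attitudes, subjective norms and "perceived level of control over childbearing behavior will be compared with before the intervention", in order to see whether couples leave pre-contemplation. The stage form is also used on both sides of the boundary. It decides entry, and then "After the intervention, each participant's level of change toward the next steps in behavioral intentions will be measured using this questionnaire".

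The design has a concurrent control: "This study is a parallel group clinical trial". On size, "we plan to recruit 15 couples per group and a total of 30 couples study participants".

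The Statistical analysis section names an ANOVA as the test of effectiveness but does not say whether the tested term is group, time or group by time. For non-normal variables it names the Friedman test. The significance level is 0.05.

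**The concern.** Attitude to having children, perceived social expectation and stage of intention are self-reports that could plausibly be answered differently face to face in a health centre and remotely through a link. If they are, the whole of that difference falls between S0 and S1, which is also where the intervention falls. A reader of within-arm results would count it as change after the intervention.

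This matters because the article's own wording leans on that contrast. Trial design describes after against before. Both primary outcomes are worded as change. The non-normal fallback is a test over time that does not compare arms. The planned validation work (internal consistency, content validity, face validity) does not address whether the two modes give equivalent answers.

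**Working it through.** **Step 1: is mode separable from period?** Code each wave from the Data collection section.

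| Wave | S0 | S1 | S2 | S3 |
|---|---|---|---|---|
| After the intervention (0/1) | 0 | 1 | 1 | 1 |
| Online (0/1) | 0 | 1 | 1 | 1 |

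The two rows are identical. Within an arm, mode and period are fully aliased, and no within-arm model can estimate one apart from the other. Dropping S2, as in the Abstract, changes nothing.

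**Step 2: what each contrast estimates.** Let *m* be the mode shift in SD units of the score, *t* any time or retest effect, and *e* the intervention effect.

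- Mean change, intervention arm: *e + t + m*
- Mean change, control arm: *t + m*
- Within-arm reading of the intervention arm: *e + t + m*, so *m* is included in full
- Between-arm difference in change: *(e + t + m) − (t + m) = e*, so a common *m* cancels

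**Step 3: size, by illustration.** The article states no figure to reproduce here. From the documents: 15 couples per arm and a significance level of 0.05. Assumed, because the documents give neither: *m* = 0.1, 0.2, 0.3 or 0.5 SD; baseline-to-follow-up correlation *r* = 0.5 or 0.7; *e* = *t* = 0; one score per couple.

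The SD of a change score is √(2(1 − r)), which is 1.000 at r = 0.5 and √0.6 = 0.775 at r = 0.7. The noncentrality of a paired t-test is m√n / √(2(1 − r)). For example, with n = 15 and m = 0.2:

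- r = 0.5: 0.2 × 3.873 / 1.000 = 0.77
- r = 0.7: 0.2 × 3.873 / 0.775 = 1.00

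Simulated rejection rates with no true effect (20,000 runs per setting, two-sided 0.05, n = 15 per arm):

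| Assumed shift (SD) | Within arm, r = 0.5 | Within arm, r = 0.7 | Between arms, r = 0.5 | Between arms, r = 0.7 |
|---|---|---|---|---|
| 0 | 5.0% | 4.9% | 4.7% | 5.3% |
| 0.1 | 6.5% | 7.7% | 4.8% | 5.1% |
| 0.2 | 11.4% | 15.5% | 4.9% | 5.2% |
| 0.3 | 19.4% | 28.7% | 5.0% | 4.8% |
| 0.5 | 43.9% | 64.9% | 5.0% | 4.8% |

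The Monte Carlo standard error at 5% is √(0.05 × 0.95 / 20,000) = 0.15 percentage points, so the between-arm columns agree with 5%.

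With the 12 couples per arm left after the planned 20% attrition (15 × 0.8 = 12), the within-arm rates at 0.2 SD are 9.8% and 13.2%, and at 0.5 SD 35.1% and 53.8%. Counting 30 individuals per arm would give higher rates, but it treats spouses as independent, so those figures are not relied on.

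**The case against.** The strongest reply is that the control arm exists for this purpose. Both arms appear to follow the same mode schedule, so a common shift cancels in the randomized comparison. That stands in full, and the table bears it out. A reader might infer that the trial's between-arm result is biased by the mode switch; the documents do not support this. Bias there would need a mode effect that differs by arm. One could imagine a route, since the researcher who follows up responses by phone is not blinded, but nothing in the article shows that the effect would differ.

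It can also be said that a within-arm paired t-test is nowhere named, that the unspecified ANOVA may be a between-arm test, and that an analysis plan not shown may say so. This is fair, and it is why the percentages are illustrations and not error rates of the planned analysis. It does not remove the point: Trial design describes the before-versus-after comparison, the Friedman test is within-subject, and an analysis plan cannot undo aliasing that data collection has fixed.

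Other limits also stand. The shifts are assumed, and at 0.1 SD the inflation is small. The SD calculation does not carry over to movement between stages, which is a classification. Any within-arm reading is also open to time and retest effects, which a single mode would not cure. Two further inferences are conjecture: that spouses answer together at home (the article says only that no clinic visit is needed, and does not say how spouses answered at S0), and that the switch costs precision between arms, which was not quantified.

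**Conclusion.** The point holds for within-arm change and for nothing wider. Mode and period coincide completely within each arm; this follows from the text and needs no assumption. How much it matters depends on a mode shift that the documents do not give. Under the assumed range, the false-positive rate of a within-arm test with 15 couples runs from little above nominal (6.5-8% at 0.1 SD) to serious (44-65% at 0.5 SD). The between-arm difference in change stays at about 5%, provided the shift is the same in both arms. Severity is minor to moderate: a planned comparison is confounded by design, the randomized one is not shown to be, and the confound can be removed cheaply before data are collected.

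**What to change.** 1. Administer the S0 outcome questionnaires, including the stage form, through the same Porsline form as S1 to S3, either on a tablet at the clinic or by link before allocation. The tablet aligns the form but not the place; the link aligns both.
2. State that each spouse completes the form separately at every wave, so that this too is constant over time.
3. State in the Statistical analysis section that the conclusion on effectiveness rests on the between-arm difference in change, or on follow-up scores adjusted for baseline. Report within-arm change, including any Friedman test, as descriptive only.

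Cost: the online form has to be built for follow-up in any case. Some participants may need a device or brief help at the baseline visit. The stated reason for going online, sparing participants later clinic visits, is kept. Item 3 costs only wording and is the part that protects the conclusion if baseline has already been collected in person.

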**Methods:**

Thirty couples (intervention, n = 15; control, n = 15) will be enrolled in this cluster randomized controlled trial. After collecting baseline data and separating participants in the pre-contemplation and contemplation stages based on the TTM, the samples were randomly assigned to the intervention and control groups. The intervention group will receive 60-min training based on TPB components for 4 weeks. The first follow-up assessment was performed immediately after the intervention and the final assessment 6 months later. For all 3 time assessments, three questionnaires will be used: The knowledge questionnaire, the TTM, and the TPB questionnaire. The most important consequences are changes in knowledge, attitudes, subjective norms, perceived behavioral control, and stages of intentions to have children.

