### Interventions

After receiving the ethical code from the Research Center of Tehran University of Medical Sciences, the study will begin. The educational content of this study will be prepared under the supervision of specialized professors of the university and the researcher will acquire the necessary knowledge and skills to carry out the educational program under the supervision of professors. In preparing this content, we will try to include the following: Complications due to reduced population growth, factors affecting the reduced ability to have children, effects of reduced population growth on family and society, complications of pregnancy at older ages, effects of father's age, benefits of having children, economic effects of demographic decline. The choice of the content is based on: the educational needs of the couples reflected in the studies, the cultural problems of the society, and the subjects mentioned by the Ministry of Health of Iran. After the teaching materials are prepared, their contents are scientifically evaluated by the Tehran University of Medicine professors, and after their approval, the intervention and training process will begin. Teaching classes will be conducted in 4 sessions and each session will last at least 60 min with the presence of couples (Table 1).

**Table 1 Tab1:** The content of the educational sessions based on the theory of planned behavior

session	Main purpose	Educational materials	Educational methods and time schedule
1	Improving couples’ knowledge and attitudes toward	PowerPoint Booklet (including contents of all sessions) Pamphlet of the first session	1) Introducing presenter and participants and explaining study aims (10 min) 2) Giving information on effect of advanced ages on fertility capacity of couples and the pregnancy’s complications (40 min) 3) Question and answer (10 min)
2	Addressing the role of subjective norms in childbearing	PowerPoint Pamphlet of the second session	1) Reviewing previous session (5 min) 2) Giving information related to Islamic beliefs on childbearing and the importance of having a child on the religious and social perspectives of Iran (15 min) 3) Presenter will use the psychodrama method. In this method two female volunteer who have at least one child role‐play problems and release their intense emotions in regard to the child, then the presenter will guide their subjective norms (37) (30 min) 4) Question and answer (10 min)

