3	Addressing the role of perceived behavioral control in childbearing	PowerPoint Pamphlet of the third session Video	1) Review of previous session (5 min) 2) Giving information on requirements and cares for becoming pregnant, prenatal cares, and care of newborn (30 min) 3) Presenting a short video which shows how a baby develops (5 min) Showing how to provide care during pregnancy and for newborn (10 min) 4) Showing videos of care of newborn (10 min) 5) Question and answer (10 min)
4	Addressing the behavioral intention and explaining how childbearing will change couple’s life	PowerPoint Pamphlet of the fourth session Video	1) Reviewing previous session (5 min) 2) Giving information on advantages of having a child from cultural, religious and social perspectives (10 min) 3) Showing videos of successful childbearing expression (10 min) 4) Question and answer (10 min)

Participants who meet the inclusion criteria will first complete a childbearing intentions questionnaire, which will be designed based on the stages of the change model and the samples who are in the pre-contemplation and contemplation stage will be included in the study. After this step, by accessing the Sib system “a national system that records health information of individuals”, couples who have been married for 2 years without children and meet the inclusion criteria will be selected. Then, 60 samples (30 pairs) will be selected through a random number table and will be randomly divided into 2 groups: control and intervention.

Teaching methods will include conferences, discussions, Q&A, and document distribution. During the classes, the researcher does not impose personal views and attitudes on the couple. It is explained to them that all decisions about having children are based entirely on their opinions and considerations and there is no coercion. They must also fill in the questionnaires without concern and honesty because their answers do not affect the quantity and quality of the treatment, and whenever they do not want to participate in the study, they can refuse to continue.

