#### Level of knowledge

The questions in this section are based on the material taught in the training sessions and are designed to investigate changes in the level of awareness of participants, as increasing the awareness of couples can help them make better decisions in the field of reproduction [29].

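### After baseline the knowledge test is answered remotely while, on the natural reading, only the intervention arm holds the written course content, so part of a knowledge difference may be look-up rather than learning

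*Protocol article*

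**What the plan says.** All references are to the Protocol article.

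- **Mode of testing.** Under Data collection, "Questions in the S0 phase are filled in person at the clinic", whereas "the questions asked in the questionnaire will be sent online in the later stages". The stated reason is to spare participants a clinic visit. The link goes out at an agreed time and "the researcher monitors their responses by phone".
- **Which questionnaires.** The Abstract (Methods) says: "For all 3 time assessments, three questionnaires will be used: The knowledge questionnaire, the TTM, and the TPB questionnaire". Only the demographic questionnaire is said to be completed solely in person. The Abstract counts three assessments and Data collection lists four (S0 to S3). On either count, every assessment after baseline is online.
- **Source of the items.** Under Level of knowledge: "The questions in this section are based on the material taught in the training sessions".
- **Written material.** Table 1 (Interventions) lists for session 1 a "Booklet (including contents of all sessions", and a pamphlet for each of the four sessions. The same section says "Teaching methods will include conferences, discussions, Q&A, and document distribution".
- **Who is taught.** From the Abstract: "The intervention group will receive 60-min training based on TPB components for 4 weeks". Under Blinding, training days are arranged so that the information does not reach controls, and the researcher is not blinded.
- **Rank of the outcome.** Awareness is listed under Secondary outcomes. The primary outcomes are stage of change and attitude.

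**The concern.** A knowledge test measures learning only if both arms sit it under conditions that give neither of them the answers. Here the items come from the course, the course exists in writing, and the test after baseline is taken away from the clinic. One arm has been handed that written course and the other, as far as the text allows one to tell, has not.

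The online mode is common to both arms, but the opportunity to consult the source is not. Randomisation therefore does not balance it, because the imbalance is created by the intervention itself. The S0 score was taken before any material was distributed, so adjusting for it does not help either.

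What is at stake is the reading of the knowledge result. Knowledge comes first in the Hypothesis and first among the consequences named in the Abstract. A positive result could be presented as evidence that the teaching worked when some of it came from reading the booklet during the test.

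**Working it through.** The plan gives no figure on this point, so there is none to reproduce. The check has two parts.

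**1. Do the statements combine as claimed?**

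| Link | Basis |
|---|---|
| Tests after S0 are remote | Stated, Data collection |
| The knowledge test is among them | Abstract: all three questionnaires at every assessment |
| Items follow the taught content | Stated, Level of knowledge |
| The taught content is handed out in writing | Stated, Interventions and Table 1 |
| Only the intervention group attends the sessions | Stated, Abstract |
| Controls hold no booklet | Inferred: it is session material, and Blinding aims to keep the information from controls |
| The booklet answers the items | Inferred from Level of knowledge and Table 1 together |

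The chain holds, with the last two links inferred.

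**2. How large could it be?** The documents give no item count, baseline score, SD or look-up rate. All inputs here are assumptions: 40% of items known at S0 (so 60% unknown), between-person SD 15 percentage points (variance 0.0225), no true learning, and no look-up by controls. A share p of intervention participants looks up a fraction f of the items they do not know.

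Rise in the arm mean = p × f × 0.60.

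- Low: 0.10 × 0.5 × 0.60 = 0.03, or 3 points.
- High: 0.30 × 1.0 × 0.60 = 0.18, or 18 points.

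On the baseline SD this is 0.03/0.15 = 0.2 to 0.18/0.15 = 1.2. But look-up by only some participants also widens the spread of the intervention arm:

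Variance = (1−p) × 0.0225 + p × (1−f)² × 0.0225 + p(1−p) × (0.60f)².

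- Low: 0.02025 + 0.00056 + 0.0081 = 0.0289. Pooled with the control variance: (0.0289 + 0.0225)/2 = 0.0257, SD 0.160. Standardised difference 0.03/0.160 = 0.19.
- High: 0.01575 + 0 + 0.0756 = 0.0914. Pooled: (0.0914 + 0.0225)/2 = 0.0569, SD 0.239. Standardised difference 0.18/0.239 = 0.75.

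So the range is about 0.2 to 0.75 pooled post-test SD.

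**What this does to a test at 0.05** (the level in Statistical analysis). The chance of a significant result favouring the intervention is about Φ(d√(n/2) − 1.96), with equal SDs for simplicity. With n = 15 per arm:

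- d = 0: Φ(−1.96) = 2.5%
- d = 0.25: Φ(0.685 − 1.96) = 10%
- d = 0.5: Φ(1.369 − 1.96) = 28%

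With 30 individuals per arm treated as independent, which spouses are not, the last two become 16% and 49%.

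**The case against.** The strongest reply is that the plan does have a safeguard: responses are given at an agreed time with the researcher monitoring by phone. This stands in part. Monitoring may discourage look-up, and nothing in the plan permits use of the booklet. But it is not described as preventing look-up, a phone call does not show what is open on the table, and the researcher knows the allocation.

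Second, the control condition is not described. This stands as a limit on certainty: that controls hold no booklet is an inference, though the opposite would defeat the separation described under Blinding.

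Third, the booklet is part of the intervention, so knowing its content is a legitimate effect. That is true of what participants have learned from it. It is not true of answers copied during the test, since Level of knowledge sets out to measure a change in participants' awareness.

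Fourth, test settings and respondent instructions often sit in a full protocol or manual. That is so, and their absence here is not the point. The point rests on three choices the article does state: remote testing, items drawn from the course, and distribution of the course in writing.

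A reader might go further than the documents allow:

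- **That the later tests are open-book for one arm as a fact, or that the knowledge difference is uninterpretable.** What is shown is a one-sided opportunity of unknown use.
- **That spouses answering together and the move from clinic to online bias the arm comparison.** Both apply to both arms. They mainly disturb before–after change, the comparison described under Trial design.
- **That the main result is at risk.** Stage of change and attitude have no answers to look up.
- **That the bias could reach 1.2 SD.** This is so only on the baseline SD. On the pooled post-test SD, the same assumptions give about 0.75.

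**Conclusion.** The point holds for one secondary outcome. As written, the plan gives intervention participants, and by inference not controls, access to the source of the knowledge items while they answer remotely. Part of a between-arm difference in knowledge may therefore be look-up, and the control arm and baseline adjustment do not remove it.

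Its size cannot be known from the documents. Under the stated assumptions it is 3–18 points, or about 0.2–0.75 pooled post-test SD (up to 1.2 baseline SD). Effective phone monitoring would make it smaller.

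This is a cheap improvement rather than a defect in the trial's main comparison.

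**What to change.** In Data collection and Level of knowledge, specify:

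- the same Porsline knowledge form at S0 (on a device at the clinic) and at every later assessment;
- a separate single-use link for each spouse, opened at the agreed time during the phone contact;
- a time limit on the knowledge section, with no return to items already answered;
- an instruction, identical in both arms, not to use written material or consult the spouse.

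Add a sentence that these steps reduce but do not eliminate look-up at home, and that the knowledge difference will be interpreted with that in mind. Baseline would still be taken at the clinic and later tests elsewhere, so before–after change remains subject to a difference in setting.

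The cost is a few settings in a system already chosen and a few sentences of text. A time limit may leave some items unanswered, in both arms. The intervention and the material handed out stay as they are.

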### Randomization

After checking the participants' basic information regarding the inclusion criteria, a list will be prepared, and then, to randomly divide them into two intervention and control groups, samples will be allocated into two groups based on the Random Number Table. Because interventions aim to educate people, participants cannot be blinded. The people targeted by the intervention are therefore aware of the group to which they belong.

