### Blinding

Additionally, there was no possibility of blinding the researcher due to the organization of the training sessions and the conduct of the interventions. However, medical center staff will be blinded. Blinding is also done when dividing the participants into two control and intervention groups and during the statistical analysis of the data. Training sessions for the intervention group will take place on days when people in the control group are not present at the clinic so that information is not randomly delivered to them and they do not communicate with each other. This issue will be the reason for the long process (about 2 years) of this research.

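### The unblinded researcher who teaches the classes also monitors post-baseline responses by phone, an avoidable route to bias in the self-reported outcomes

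*Protocol article*

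**What the plan says.** The Data collection section of the protocol article has the baseline form (S0) completed in person at the clinic. The later forms (S1 to S3) are sent through an online system, Porsline. A survey link goes out at an agreed time, and "the researcher monitors their responses by phone".

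Three other sections identify that researcher's role:

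- Interventions, on preparing the course: "the researcher will acquire the necessary knowledge and skills to carry out the educational program".
- Interventions, on the sessions themselves: "During the classes, the researcher does not impose personal views and attitudes on the couple".
- Blinding: "there was no possibility of blinding the researcher due to the organization of the training sessions and the conduct of the interventions".

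On the remaining blinding, the Randomization section says that "participants cannot be blinded". The Blinding section says that "medical center staff will be blinded" and adds that the allocation step and the statistical analysis are blinded. It does not mention outcome collection.

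On the outcomes, the Methods part of the abstract says that "three questionnaires will be used: The knowledge questionnaire, the TTM, and the TPB questionnaire". The Primary outcome section names movement along the stages of change and a positive attitude. Both are measured with these participant-completed forms.

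**The concern.** The person who has spent four sessions explaining the case for having children is the person in phone contact about the answers. Intervention couples know this person as their teacher. The article describes no such contact for control couples. If the calls touch on content, or if participants simply know that their teacher follows their answers, some will lean towards the taught answer. That lean would be stronger in the intervention arm and in the direction of the hypothesis.

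Randomisation does not protect against this, because the influence arises after allocation. Blinding the analyst does not remove it either, because the shift is already in the data. Both primary outcomes are exposed. The answers cannot be collected again free of this influence, so the procedure has to be settled before S1.

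**Working it through.** The article states no figure on this point, so there is none to reproduce. The check has two parts.

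**1. The roles side by side**

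| Question | What the article gives | Section |
|---|---|---|
| Who teaches? | The researcher | Interventions |
| Is that person blinded? | No, because of the teaching | Blinding |
| Who follows the answers after baseline? | The researcher, by phone | Data collection |
| Are participants blinded? | No | Randomization |
| Who or what is blinded? | Centre staff, allocation step, analysis | Blinding |
| Is outcome collection blinded or kept apart from teaching? | Not stated | – |
| Where do outcomes come from? | Knowledge, TTM and TPB questionnaires | Abstract, The study instruments |

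Teaching, knowledge of the arm and contact about the answers therefore fall to one role. Baseline is completed at the clinic, so the phone contact belongs to the assessments at which the intervention is judged.

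The exposure is uneven. Attitude, subjective norms, perceived control and stage of change ask for views or self-placement, so wishing to please can move them directly. The knowledge items test taught material, and wishing to please does little for someone who does not know the answer.

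**2. Illustration of sensitivity**

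The documents give no size for any reporting shift. Assume a shift of b = 0.2 to 0.5 SD between the arms, no true effect, a two-sided 5% t test, and n independent units per arm. The Sample size section gives n = 12 after attrition and n = 15 recruited.

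- Noncentrality = b × sqrt(n/2), with 2n − 2 degrees of freedom.
- n = 12, 22 df, critical value 2.074: b = 0.2 gives noncentrality 0.490 and a rejection rate of 0.076; b = 0.5 gives 1.225 and 0.216.
- n = 15, 28 df, critical value 2.048: b = 0.2 gives noncentrality 0.548 and a rejection rate of 0.083; b = 0.5 gives 1.369 and 0.262.

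The range is about 8% to 26%, against a nominal 5%.

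For scale, the Sample size section uses a sum of variances of 2.1664 and a squared difference of 2.6896.

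- SD = sqrt(2.1664/2) = 1.04.
- Planned difference = sqrt(2.6896) = 1.64, which is 1.64/1.04 = 1.58 SD.
- Assumed shift = 0.2 × 1.04 = 0.21 to 0.5 × 1.04 = 0.52 points, or 13% to 32% of the planned difference.

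These planning values come from an intention score in a cited similar study, not from the attitude or stage outcomes of this trial.

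**The case against.** The strongest reply is that monitoring responses, in a sentence about sending a link so that people need not come to the clinic, may mean only checking that forms come back. That reading is open, and a reader should not infer that the article has the researcher listening to or discussing answers. Call scripts and access rights are also details that an article may leave to a full protocol. What stands is that the article does assign this contact to the unblinded teacher, speaks of responses, and sets no limit on it.

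Four further points are fair, and they bound the finding:

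- **Not every outcome equally.** A reader might infer that all outcomes are equally compromised. Knowledge is tested on taught content and is less exposed.
- **Not strictly one arm.** The objectives are explained to all participants before consent, and the phone contact is not described differently by arm. Control couples may also sense the preferred answer. A difference between arms is probable, but zero pressure among controls is not established.
- **The figures do not measure the phone contact.** Participants know their arm, and self-report after persuasive teaching carries desirability bias whoever sends the reminders. The 0.2 to 0.5 SD shift has no source in the documents and stands for the total. Against a planned effect of about 1.58 SD, it would not account for the whole.
- **Partial safeguards exist.** The Interventions section has the researcher refrain from imposing views, rules out coercion and asks for honest answers. Completion online is less exposed than a face-to-face interview. These reduce the risk but do not separate the teacher from outcome collection.

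The possibility that the presenter in Table 1 is someone else would weaken the point. However, the Interventions and Blinding sections tie the researcher to the teaching.

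**Conclusion.** The point holds as a design weakness that should be corrected before the first post-baseline assessment. The article has the unblinded teacher monitor responses at the post-baseline assessments, does not limit this to completion, and states no blinding for outcome collection. This adds an avoidable route to social-desirability bias. It would probably favour the intervention, mainly on attitude, subjective norms, perceived control and stage of change, and less on knowledge.

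Its size cannot be derived from the documents. The false-positive range of about 8% to 26% rests on the assumed 0.2 to 0.5 SD shift, no true effect and 12 to 15 independent units per arm. It illustrates total self-report bias, only part of which the phone contact could cause or the fix could remove. The conclusion also assumes that the researcher in the Data collection section is the one who teaches.

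**What to change.** In the Data collection section, replace the clause on phone monitoring with text to this effect:

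- Participants complete each form privately in Porsline under a study code.
- Reminders are the same in both arms and concern completion only. They are preferably sent automatically. Otherwise they follow a fixed script and come from someone not involved in teaching.
- The researcher who teaches does not discuss items and has no access to answers until the last S3 form is in.

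Two details need care. Participants know their arm, so a call may unblind the caller. If blinded centre staff were used, this should be acknowledged, and it is why automatic reminders are preferable. The Statistical analysis section has questionnaire data entered into SPSS at each stage, so that entry should be done by someone other than the teaching researcher or by coded export. The Blinding section should then state how outcome collection is handled.

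The cost is minor: set-up of reminders, or some staff time for 60 people at three follow-ups, plus the data-entry arrangement. Bias from participants knowing their arm will remain and should be named as a limitation.
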